### Statistical Analysis

Statistical analysis will be performed using IBM SPSS version 28 (IBM Corporation, Armonk, NY, USA). Intention-to-treat analysis of between-group changes at the end of the initial intervention/control period will use linear mixed effects model analysis of variance for the primary and secondary outcome measures, with adjustments for any statistically significant differences in baseline covariates between the groups. Maximum likelihood estimation through the linear mixed effects model analysis of variance will be used for missing data. Following an intention-to-treat analysis, a “per protocol” analysis will be undertaken using the same statistical methods. Post-hoc analyses will also be undertaken to establish characteristics of responders to the intervention. Analysis of the data from the cross-over group will use repeated measures analysis of variance to evaluate the within-group change due to the intervention. Data analysis at the 12-month follow-up will be exploratory. If adequate numbers in the control group do not cross-over to the intervention, a between-groups analysis will be undertaken. However, it is anticipated that the majority of participants in the control group will cross-over into the IG, in which case the analysis will evaluate the change from completion of the intervention to the 12-month timepoint. The level of significance for all outcomes will be set at an alpha of <0.05.

The semi-structured interviews will be transcribed and coded using NVivo 9 (QSR International, Melbourne, Vic., Australia). Thematic and descriptive qualitative analysis^40^ will be used to identify key themes regarding participant opinions, and perceived barriers and facilitators to participation in the telerehabilitation program. At least 3 investigators will review the coding to ensure it is insightful. Any discrepancies will be discussed by the research team and the coding revised accordingly.

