**Methods:**

The study will be a multi-site randomized controlled trial with assessor blinding. Participants with confirmed previous COVID-19 infection and persistent respiratory symptoms who attend a post-COVID respiratory clinic will be randomized 1:1 to either an intervention group of 4 weeks, twice-weekly pulmonary telerehabilitation or a control group of usual medical care. Participants in the control group will be invited to cross-over into the intervention group after the week 4 assessment. Primary outcome: exercise capacity measured by the 1-minute sit-to-stand test. Secondary outcomes: 5 repetition sit-to-stand test; Montreal Cognitive Assessment; COVID-19 Yorkshire Rehabilitation Scale; Chronic Obstructive Pulmonary Disease Assessment Test; 36-Item Short-Form Health Survey; Hospital Anxiety and Depression Scale; Fatigue Severity Scale; and the Kessler Psychological Distress Scale. Outcomes will be collected at baseline, after 4-weeks intervention or control period, after intervention in the cross-over group, and at 12-month follow-up.

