### Sample Size

A total of 42 participants will be required to have an 80% chance of detecting, as significant at the 5% level, a between-group difference of 3.5 repetitions in the 1-minSTST (primary outcome), which is the minimal clinically important difference, using a standard deviation of 4 repetitions.^23^ To account for a 15% dropout, 48 participants will be recruited.

The sample size for the semi-structured interviews will be approximately 15 to 20 participants. Interviews will continue until thematic saturation.

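### Covariates for the primary and secondary models are chosen by baseline significance tests, so the model is not fixed in advance and baseline 1-minSTST, age and sex would enter only by chance

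*Protocol article*

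**What the plan says.** The Statistical Analysis section sets the main analysis as follows: "Intention-to-treat analysis of between-group changes at the end of the initial intervention/control period will use linear mixed effects model analysis of variance". It covers the primary and all secondary outcomes and is to be run "with adjustments for any statistically significant differences in baseline covariates between the groups". No covariate is named as a fixed term. The section does not say whether the baseline value of an outcome enters as a subtracted value, as a repeated response or as a covariate. Nor does it say whether the arms' baseline means are constrained to be equal.

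The section gives no separate threshold for the baseline tests; the only one stated is for the outcomes: "The level of significance for all outcomes will be set at an alpha of <0.05". I take 5%, two-sided, for the baseline tests as well.

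The Study Design section describes a concealed, computer-generated sequence with minimisation on age (50 or below against above 50) and sex. The Outcome Measures section has baseline outcomes collected at an initial videoconference assessment.

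**The concern.** When allocation is concealed and random, any baseline difference between arms is due to chance. A p-value for that difference says nothing about whether the variable predicts the outcome, and that prediction is the reason to adjust. The rule therefore selects on the wrong property. It can admit a variable unrelated to 1-minSTST that happened to differ, and pass over a strongly prognostic one that happened to be balanced.

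Three things follow.

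- The confirmatory model is not known until baseline data have been compared by arm. No list says which variables are to be tested.
- Age and sex, which the investigators thought important enough to minimise on, are balanced by that step and so would almost never qualify.
- The baseline value of the outcome, usually its best predictor, is not guaranteed a place as a covariate. At stake is precision in a trial of 42 evaluable participants with little power to spare.

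**Working it through.** **Inputs from the protocol article.** Sample Size section: "A total of 42 participants will be required to have an 80% chance of detecting", as significant at 5%, "a between-group difference of 3.5 repetitions in the 1-minSTST (primary outcome", "using a standard deviation of 4 repetitions". Abstract, Methods: participants "will be randomized 1:1 to either an intervention group" or usual care. Two assumptions are needed. The test is taken as two-sided. The correlation r between baseline and week-4 scores is not given, so it is shown at 0.5, 0.7 and 0.8. The article also does not say whether the SD of 4 belongs to the week-4 score or to the change, so both readings are worked. Score SDs are taken as equal at the two visits.

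**1. The plan's own figure.** n per arm = 2 × (1.960 + 0.842)² × 4² / 3.5² = 20.5, rounded up to 21, so 42 in total. The stated figure reproduces with no baseline adjustment. The standard error is 4 × √(2/21) = 1.234, and 3.5/1.234 = 2.835. Power is Φ(2.835 − 1.960) = 0.809 by the normal approximation, and 0.790 by the noncentral t with 40 degrees of freedom.

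**2. How often the rule selects something.** A 5% test of a variable whose true difference is zero is significant in 5% of trials. In simulation at 21 per arm (20,000 runs per scenario, simple randomisation), baseline 1-minSTST was selected in 4.9% to 5.1%. If k independent covariates are tested, the chance that at least one enters is 1 − 0.95^k: 23% for k = 5, 40% for k = 10, 54% for k = 15. The article gives no k, so these are illustrations.

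**3. Change analysis against baseline adjustment.** With score SD σ, the variance of change is 2σ²(1 − r), and the residual variance after baseline adjustment is σ²(1 − r²). The ratio of the second to the first is (1 + r)/2. Estimating the slope multiplies the adjusted variance on average by 1 + 1/(2×21 − 4) = 1 + 1/38, and leaves 39 degrees of freedom. Power below is from the noncentral t.

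*SD 4 is the SD of change.* Adjusted residual SD = 4√((1 + r)/2).

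| r | Residual SD | Power, change | Power, adjusted |
|---|---|---|---|
| 0.5 | 3.46 | 79% | 88% |
| 0.7 | 3.69 | 79% | 84% |
| 0.8 | 3.79 | 79% | 82% |

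*SD 4 is the SD of the week-4 score.* Change SD = 4√(2(1 − r)); adjusted residual SD = 4√(1 − r²).

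| r | Change SD | Residual SD | Power, change | Power, adjusted |
|---|---|---|---|---|
| 0.5 | 4.00 | 3.46 | 79% | 88% |
| 0.7 | 3.10 | 2.86 | 95% | 97% |
| 0.8 | 2.53 | 2.40 | 99% | above 99% |

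On the second reading the gain is about 9 points, 2 points and negligible.

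**4. The rule itself.** I take a change analysis as the default, with a switch to baseline adjustment only when the baseline test is significant, and score SD 4. The simulated type I error was 0.045, 0.046 and 0.047 at r = 0.5, 0.7 and 0.85. Power was 0.80, 0.95 and above 0.99. The rule behaves almost exactly like the plain change analysis, because it rarely switches.

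**The case against.** The strongest reply is that the model already uses baseline. The article analyses between-group changes in a mixed model, so the baseline score probably enters by subtraction or as a repeated response, whatever the covariate clause selects. The words on baseline covariates may refer to other characteristics altogether. If the arms share a common baseline mean, the model is nearly equivalent to covariate adjustment and most of the loss disappears.

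This stands, and it rules out several stronger readings that a reader might infer.

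- *Baseline adjustment is lost, or the baseline data are thrown away.* The text does not support this. Baseline is probably used, though less efficiently than it could be.
- *Chance imbalance in 1-minSTST goes uncorrected.* A change score subtracts the whole gap. What remains is over-correction of (1 − r) times the gap: for 2.5 repetitions, 1.25, 0.75 and 0.5 at r = 0.5, 0.7 and 0.8.
- *A baseline gap must exceed 2.5 repetitions before it is adjusted for.* That figure, 2.021 × 4 × √(2/21) = 2.49, takes 4 as the baseline SD. If 4 is the SD of change, the baseline SD is 4/√(2(1 − r)), and the threshold is 2.5 only at r = 0.5. It is 3.2 at r = 0.7 and 3.9 at r = 0.8.
- *The false-positive rate is inflated, or 42 is too few.* Step 4 shows a slightly conservative test, and step 1 reproduces 42 without any baseline adjustment.

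It is also fair to say that admitting a non-prognostic covariate by chance does little harm: about one degree of freedom and a little precision, with no bias.

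The reply does not rescue the clause. The article states the selection rule outright, so this is not a detail left to a fuller document. An analysis plan that followed the rule would inherit the problem, and one that did not would contradict the published protocol.

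**Conclusion.** The point holds under every reading of the model: covariates for the primary and secondary analyses are chosen by tests that detect only chance, and the confirmatory model is not fixed before arm-level data are seen. Neither the outcome's baseline value nor the minimisation factors are guaranteed a place as covariates.

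The cost is in efficiency and prespecification; validity is not in doubt. It ranges from about 9 points of power at r = 0.5 to about 3 points (SD 4 as change) or almost nothing (SD 4 as week-4 score) at r = 0.8. These figures rest on an assumed correlation, equal SDs at both visits, 21 evaluable participants per arm, and a default analysis with no common baseline mean. The loss is measured against what the same data could deliver; the power the plan set out to have is essentially met. This should be fixed, but it does not undermine the trial.

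**What to change.** Delete the clause that makes adjustment depend on significant baseline differences. In its place, prespecify one model for every outcome that includes that outcome's own baseline value for all participants, either as week-4 ANCOVA or as a mixed model with a common baseline mean across arms. Add age group and sex, the minimisation factors, as fixed terms. State that no covariate will be selected by baseline testing. Say also whether the SD of 4 repetitions is that of the week-4 score or of the change, so that the gain can be judged.

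The cost is a sentence or two in the analysis section. It needs no new data, visits or participants, and should be done before anyone sees outcome or baseline data by arm.

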### Control Group

The control group will receive usual medical care as well as a copy of the WHO Pamphlet.^21^ At the end of the 4-week control period, participants in the control group will be invited to cross-over into the IG. The cross-over is to encourage recruitment since the advice from those with lived experience of PCS was that participants needed the option to receive telerehabilitation after the control period. Additionally, as research in telerehabilitation for PCS is currently very limited, the crossover will provide increased data on rehabilitation outcomes.

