Several prospective cohort studies have demonstrated the effectiveness of face-to-face outpatient rehabilitation on PCS symptoms, exercise capacity, and HRQoL,^54–57^ although, since these studies were not RCTs, the effect of natural recovery is unknown. A number of RCTs have evaluated exercise interventions. One study evaluated an unsupervised 6-week, home-exercise program delivered via smartphone and demonstrated improvements in strength and HRQoL^58^; 2 separate inspiratory muscle training trials of 8 and 12 weeks, respectively, demonstrated improvement in breathlessness, exercise capacity, and HRQoL compared with usual care for people reporting post-COVID dyspnea^59^^,^^60^; and a trial evaluating very short duration (10 minutes) “respiratory rehabilitation” involving the use of a threshold positive expiratory pressure device, forced repeated coughing exercise (3 sets of 10 coughs), diaphragmatic breathing, and upper limb dynamic stretching, demonstrated improvements in respiratory function, HRQoL, and anxiety.^61^ The rationale for this study is that there are no published RCTs that have evaluated telerehabilitation including exercise training (similar to that which is provided in a PR program) and education for people with PCS with specific respiratory sequelae. The importance of the study is that, due to the high prevalence of people with PCS, robust research is needed to investigate rehabilitation programs that address the debilitating symptoms of PCS.

The optimal length of rehabilitation programs for people with PCS is unknown. We have chosen to evaluate a short-duration (4-week) program. A number of studies of exercise training provide evidence of improvements in exercise capacity and quality of life in short-duration programs.^62^^,^^63^ For example, in people with PCS, intensive PR of 3 weeks was effective in improving exercise capacity and quality of life (although this was a 5 day per week intervention)^57^ and a 4-week unsupervised program with video-assisted, individualized exercises demonstrated improvements in functional capacity.^63^ Additionally, in people with chronic obstructive pulmonary disease, the greatest statistically significant improvements in exercise capacity occurred within the first 4 weeks of a PR program.^62^ The short duration may also be more acceptable to those with PCS who remain in the workforce with limited time for rehabilitation.

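### The cross-over group's before-after change is attributed to the programme, although with no concurrent untreated group it cannot be separated from natural recovery

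*Protocol article*

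**What the plan says.** Controls are invited to take up the programme after the week-4 assessment. The Control Group section gives recruitment as the first reason for this and adds that "the crossover will provide increased data on rehabilitation outcomes". For these participants the Statistical Analysis section specifies: "Analysis of the data from the cross-over group will use repeated measures analysis of variance to evaluate the within-group change due to the intervention". It names no comparator. The same section calls only the 12-month analysis exploratory and closes with "The level of significance for all outcomes will be set at an alpha of <0.05". According to the abstract, cross-over participants are assessed at baseline, at week 4, after their own programme, and at 12 months.

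Elsewhere the article recognises the problem. On earlier uncontrolled cohorts the Discussion remarks that "since these studies were not RCTs, the effect of natural recovery is unknown". The section on patient-reported outcomes names natural recovery in controls who stay untreated as something to be evaluated at 12 months.

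**The concern.** The stated aim of the cross-over analysis is causal, but the data are uncontrolled. A change from week 4 to the end of the programme is the sum of whatever the programme does and whatever would have happened anyway. In people recovering from COVID-19 the second part may not be zero, and the article expects that it may not be. If the whole change is credited to the programme, an ineffective programme can look effective in this group. The article would then rely on the kind of evidence that it discounts in other studies. This concerns what the plan states about the meaning of the change, not a detail left to a fuller document.

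**Working it through.** **The plan's own figure first.** Sample Size gives "an 80% chance of detecting, as significant at the 5% level" for a difference of 3.5 repetitions, "using a standard deviation of 4 repetitions". With the normal approximation, n per arm = 2 × (1.960 + 0.842)² × 4² / 3.5² = 20.5, so 21 per arm and 42 in total, as stated. (A t-based calculation gives 22 per arm, with power 79.0% at 21; this is not material here.) That figure belongs to the randomised comparison. No size, power or expected change is given for the cross-over analysis.

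**Inputs for the check**
- Number crossing over: 48 recruited and randomised 1:1 gives 24 controls; less 15% dropout, 24 × 0.85 = 20.4, taken as 20. This assumes that nearly all retained controls cross over; the article expects a majority.
- SD of change: 4 repetitions. The article does not say whether its SD of 4 refers to scores or to change, so this is an assumption.
- Test: two-sided 5%. The article does not state sidedness.
- True programme effect: 0.
- Drift over the programme weeks: not given in the documents, so a range is shown.

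**False attribution rate.** With two visits the repeated measures ANOVA is a paired t-test. The standard error is 4/√20 = 0.894, the critical value on 19 degrees of freedom is 2.093, and the noncentrality is drift/0.894.

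| Drift (repetitions) | Noncentrality | Probability of a significant improvement |
|---|---|---|
| 0 | 0 | 2.5% |
| 0.5 | 0.56 | 7.7% |
| 1 | 1.12 | 18.5% |
| 2 | 2.24 | 56.4% |

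**Sensitivity.** With 12 cross-over participants the figures for 1 and 2 repetitions are 12% and 35%; with 24 they are 22% and 65%. If 4 is the SD of scores and visits correlate at r = 0.5 to 0.8, the SD of change falls from 4.0 to 2.53. At n = 20 the rates for 0.5, 1 and 2 repetitions then become 8–13%, 19–39% and 56–92%.

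**What a within-person comparison would do.** Take the change on the programme minus the same person's change over weeks 0 to 4. With equal correlation between visits and an SD of change of 4, the error variance per visit is 4²/2 = 8. The contrast (post − 2 × week 4 + baseline) has variance (1 + 4 + 1) × 8 = 48, so its SD is 6.93.
- 95% half-width for the simple change: 2.093 × 4/√20 = 1.87.
- 95% half-width for the difference of changes: 2.093 × 6.93/√20 = 3.24.
- With equal drift in both periods the drift cancels, and the two-sided false-positive rate is 4.8–5.3% in simulation.
- With drift slowing from 2 to 1 repetition, the contrast is centred on 1 − 2 = −1. It rejects in 9.6–16.1% of trials (r = 0.5 to 0.8), almost always against the programme.
- Power for a true effect of 3.5 repetitions is 57% at r = 0.5, 79% at r = 0.7 and 93% at r = 0.8.

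**The case against.** The efficacy question does rest on the randomised comparison. The aim, the conditional impact statement, the sample size and the primary analysis are all framed as programme against usual care. The clause at issue is one sentence about a supplementary analysis in a condensed article, and it says that the change will be evaluated, not how it will be reported. All of that stands, and it limits the weight of the point. It does not remove it, because the causal attribution is in the article's own words and the analysis is not among those called exploratory.

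Three stronger readings are tempting and are not supported.
- A reader might infer that a three-visit ANOVA would be judged on its overall time test, which change in the untreated weeks alone could make significant. The article does not say which visits enter or which test is read, and such detail may properly be left to a fuller document.
- A reader might add regression to the mean. Entry has no score threshold, all controls are invited, and most are expected to accept, so selection on poor week-4 scores is probably limited.
- A reader might give much weight to retest gain. By the post-programme visit participants have done the 1-minute sit-to-stand test at screening, baseline and week 4, so further learning should be smaller, and the cognitive test uses alternative versions. Natural recovery is the substantive bias.

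It is also fair to say that the inflation figures depend wholly on assumed drift. At 0.5 repetitions the excess is modest.

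**Conclusion.** The point holds as an error in the stated aim of one supplementary analysis. A within-group change in which everyone is treated cannot be described as the effect of the programme, and the article makes that argument itself about other studies. Under 20 participants, an SD of change of 4 and no programme effect, the chance of a significant improvement is about 8%, 18% or 56% for drift of 0.5, 1 or 2 repetitions, instead of 2.5%. The conclusion itself needs no figure; only the size depends on these assumptions.

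A reader might infer that the trial's main result is compromised, or that the protocol commits to presenting the cross-over result as confirmation of it. Neither follows. The between-group comparison at the end of the initial period is a separate analysis and is unaffected, and the documents contain no such reporting rule.

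**What to change.** In the Statistical Analysis section:
1. Replace the causal phrase at the end of the cross-over sentence with *over the programme period*.
2. Label the cross-over analysis supportive, and state that claims of effect rest on the randomised week-4 comparison.
3. Report the week-4 to post-programme change beside the same participants' change over weeks 0 to 4, with the difference between the two and its 95% CI.
4. Note the limit of that contrast: it removes drift only if drift is equal in both periods. If recovery slows, a bias remains, and it then runs against the programme.

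The data are already to be collected, so the cost is wording and one extra contrast. The downside is a weaker claim and a wider interval: half-width about 3.2 repetitions for the difference of changes against 1.9 for the simple change, at n = 20 under the same assumptions and equal correlation between visits.

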### Outcome Measures

Following recruitment, baseline outcomes will be collected at an initial videoconference assessment. At all follow-up assessment times (Figs. 1 and 2), the physical outcomes will be collected by a physical therapist who is blind to group allocation. Participants will be asked not to divulge their group allocation. Outcome measures are outlined below.

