#### Patient Reported Outcomes

The following questionnaires will be emailed to the participant through REDCap and will be completed at each assessment timepoint (Fig. 2). Participants in both groups will be asked to complete a weekly symptom diary via REDCap.

HRQoL will be measured using the 36-Item Short-Form Health Survey (SF-36)^31^ which comprises 36 questions across 8 domains of health. Anxiety and depression will be measured using the Hospital Anxiety and Depression Scale^32^ and the Kessler Psychological Distress Scale (K6+).^33^ The Hospital Anxiety and Depression Scale is a 14-item validated questionnaire^34^ and the K6+ is a reliable and valid 6-item questionnaire.^35^ Fatigue will be measured using the 9-item Fatigue Severity Scale^36^ which measures both severity of an individual’s fatigue and the effect of fatigue on their activities of daily living. Respiratory symptoms will be measured using the Chronic Obstructive Pulmonary Disease Assessment Test.^37^ Although designed for people with chronic obstructive pulmonary disease, the Chronic Obstructive Pulmonary Disease Assessment Test is widely used for many respiratory conditions as a measure of the presence and severity of respiratory symptoms such as breathlessness, cough, chest tightness, and sputum production.

Composite outcomes will be measured using the COVID-19 Yorkshire Rehabilitation Scale (YRS-19)^38^ which is a comprehensive COVID-specific patient reported measure that provides a score for several outcomes related to the domains of “symptoms severity” and “functional disability”.

At the 12-month follow-up assessment, participants will be asked to complete all previous assessments as well as the return-to-work questions from the International Severe Acute Respiratory and emerging Infection Consortium (ISARIC) questionnaire.^39^ The 12-month follow-up is exploratory and will evaluate any ongoing effects of the intervention, as well as natural recovery in participants in the control group who did not cross-over.

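### The cross-over analysis attributes an uncontrolled within-group change to the programme, without a caveat, in controls who chose to cross over

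*Protocol article*

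**What the plan says.** The Statistical Analysis section of the protocol article specifies a linear mixed effects model, with maximum likelihood for missing data, for the randomised comparison after the first four weeks. It names a different method for the cross-over group: the analysis "will use repeated measures analysis of variance to evaluate the within-group change due to the intervention". A significance level of 0.05 applies to all outcomes. Only the 12-month analysis is called exploratory.

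The Control Group section describes how people enter this group: after the four control weeks, "participants in the control group will be invited to cross-over into the IG". It gives two reasons. The offer helps recruitment, and "the crossover will provide increased data on rehabilitation outcomes". The Abstract lists the assessments as baseline, then "after 4-weeks intervention or control period, after intervention in the cross-over group, and at 12-month follow-up".

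Two other places bear on natural recovery. On earlier prospective cohorts, the Discussion remarks that "since these studies were not RCTs, the effect of natural recovery is unknown". The Patient Reported Outcomes section says that the 12-month follow-up will evaluate, among other things, "natural recovery in participants in the control group who did not cross-over".

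**The concern.** The last four words of the cross-over sentence make a causal claim that the design cannot support. Those analysed are controls who accepted an offer, and no untreated group is followed over the same weeks. Their change from week 4 to the end of the programme has at least four possible sources: the programme, natural recovery, gain from repeating the test, and selection. Selection matters because acceptance may depend on how a person feels at week 4, and people who accept when they feel worse than usual tend to improve anyway.

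The article treats natural recovery as an open question in this condition and marks down other groups' non-randomised studies for it. A reader of the results could take a significant cross-over change as a second, independent demonstration of benefit, although it could arise with no programme effect at all.

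**Working it through.** **The plan's own figure.** The sample size is not in dispute, but it shows how many controls there will be. With a difference of 3.5, SD 4, 80% power and two-sided 5% (two-sidedness assumed):

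n per arm = 2 × (1.960 + 0.842)² × 4² / 3.5² = 2 × 7.85 × 1.306 = 20.5, rounded up to 21, so 42 in total, as stated.

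With 48 recruited 1:1, there are 24 controls randomised and about 21 evaluable. The article expects most of them to cross over but gives no number.

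**What the within-group change estimates.** Write θ for the programme effect, r1 for the non-programme change (recovery, retest, selection) from baseline to week 4, and r2 for the same from week 4 to the end of the programme.

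- Expected control-period change: r1
- Expected cross-over-period change: θ + r2

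The second equals θ only if r2 = 0. The article nowhere argues that r2 is zero, and its remarks on natural recovery point the other way.

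**How often drift alone gives p<0.05.** Set θ = 0 and test the week-4-to-post-programme change with a two-sided paired t-test at 5%. The noncentrality is r2 / (s/√n), where s is the SD of change.

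The documents give no value for n, s or r2, so all three are assumed. A change SD of 4 corresponds to a visit SD of 4 with correlation 0.5, since 4 × √(2 × 0.5) = 4. A change SD of 3.1 corresponds to correlation 0.7, since 4 × √(2 × 0.3) = 3.1.

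For n = 20 and s = 4, s/√n = 0.894. The noncentrality is 1.12, 1.68 and 2.24 for r2 = 1, 1.5 and 2.

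| n | s | r2 = 0 | r2 = 1 | r2 = 1.5 | r2 = 2 |
|---|---|---|---|---|---|
| 16 | 4 | 0.05 | 0.155 | 0.290 | 0.465 |
| 20 | 4 | 0.05 | 0.186 | 0.357 | 0.565 |
| 24 | 4 | 0.05 | 0.217 | 0.421 | 0.650 |
| 16 | 3.1 | 0.05 | 0.227 | 0.441 | 0.675 |
| 20 | 3.1 | 0.05 | 0.278 | 0.538 | 0.782 |
| 24 | 3.1 | 0.05 | 0.329 | 0.622 | 0.857 |

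The direction needs no assumed values: any non-zero r2 lifts the rejection rate above 5% when θ = 0.

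**What the control period can add.** The difference between the two changes has expectation θ + (r2 − r1). It equals θ only if recovery and retest gain are the same in both periods. If they slow, r2 < r1 and the difference understates θ.

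With equal SD σ and equal correlation ρ between visits (assumed), the variance of one change is 2σ²(1 − ρ) and that of the difference is 6σ²(1 − ρ). The standard error is therefore √3 = 1.73 times as large. At n = 20 and s = 4 it rises from 0.89 to 1.55 repetitions.

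**The case against.** The strongest reply is that this is one phrase in a supplementary analysis. The efficacy conclusion rests on the randomised week-4 comparison. The article gives recruitment and additional data as the reasons for the cross-over, and nowhere says that the result will be presented as confirming efficacy. The sentence itself says within-group change. The same people also have an untreated four-week period, so a repeated measures analysis over three visits could compare the two periods, and the choice of contrast may be left to an analysis plan that is not shown. All of this stands and limits the consequence. It does not remove the stated attribution, which the article makes without a caveat.

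The illustrative rates are also open to challenge. They are the power of a paired test to detect a real but non-programme change; they are not a type I error rate for the hypothesis of no change. Every participant will also have done a supervised sit-to-stand test at screening, so retest gain this late may be small. That is fair: the figures show sensitivity and do not estimate what will happen.

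Three stronger readings may tempt a reader, and the documents do not support them.

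- *The article concedes that recovery cannot be separated in such data.* It says only that the effect is unknown in other groups' cohort studies. Applying that reservation here is an inference from the shared non-randomised, pre-post form, and this group has a control period that those cohorts may have lacked.
- *The assessor is unblinded at the post-cross-over visit.* The Outcome Measures section says that at all follow-up times "the physical outcomes will be collected by a physical therapist who is blind to group allocation". Only treated controls have that extra visit, but the assessor learns the arm only by knowing which visit it is. Participants are asked not to disclose allocation, and the visit figures are not shown. This is a risk and no more.
- *Participants with a missing visit will be dropped.* This is a property of the standard form of the named method. The article does not say how missing cross-over visits are handled.

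**Conclusion.** The point holds as a fault in the stated interpretation. The article attributes the cross-over group's change to the programme, but the design gives a change in which programme effect, recovery, retest gain and selection are not separated. This follows from the one-way voluntary entry and the lack of a concurrent comparator, and needs no numerical assumption.

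Its size cannot be fixed from the documents. With 16 to 24 people crossing over and a change SD of 3.1 to 4, an assumed non-programme gain of 1 repetition gives significance in about 16% to 33% of trials with no programme effect, and a gain of 2 repetitions in about 47% to 86%.

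The randomised comparison, its sample size and its blinding are not called into question. The wording should be changed before the results are written up, but the trial's main conclusion does not depend on it.

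**What to change.** In the Statistical Analysis section, end the cross-over sentence with the uncontrolled within-group change in place of the causal phrase, and label the analysis exploratory and non-randomised.

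Estimate it with the linear mixed model already specified for the main analysis, over baseline, week 4 and post-programme. Report the change from week 4 to post-programme beside the change from baseline to week 4, with the number who declined to cross over. State whether those who declined are in the model. If they are, their post-programme values are never observed, and the estimate then rests on an untestable missing-data assumption that should be named.

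If the difference between the two changes is reported, say that it assumes equal recovery and retest gain in both periods and would understate the programme effect if these slow.

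No new data are needed. The cost is wording, one extra estimate and a more cautious claim. The difference, if reported, also has a wider interval, about 1.7 times as wide as that of the single change under the equal-correlation assumption above.
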